### Agreement statistics

The inter-rater and intra-rater agreement of the recommendation of EVT will be assessed using Gwet’s AC1 (κ_G_) reliability coefficient. AC1 stands for agreement coefficient, first order chance correction and is used for binary data [39]. We will derive the κ_G_ for binary (EVT recommendations) data, with 95% bias-corrected confidence intervals. Poor (κ_G_ <0), slight (κ_G_ = 0–0.20), fair (κ_G_ = 0.21–0.40), moderate (κ_G_ = 0.41–0.60), substantial (κ_G_ = 0.61–0.80) and excellent (κ_G_ >0.80) agreement categories were defined according to Landis and Koch and used to classify the K_G_ [40]. Non-overlapping confidence intervals along with level of agreement will be the factors considered to suggest a potential difference between KG values [41]. Reliability calculations will be done according to the following prespecified rater subgroups for interrater reliability: rater specialty, rater experience, infarct core size and time since stoke onset. For intrarater reliability we will look at rater specialties. We will use the R statistical computing language (R Core Team, 2022) in the RStudio framework to compute for the K_G_ values using the irrCAC package [42].

Classically, the Kappa statistic was used to quantify the degree of reliability between raters [43]. Cohen’s Kappa was computed by the following equation: (observed agreement-expected agreement)/ (1-expected agreement). The Kappa paradox arises in situations where the prevalence of the “condition” is high such that the likelihood of agreeing to diagnose the presence of absence of a disease (or recommend EVT as in our study) between raters is very high or very low. In this cirumstance the kappa statistic is disproportionately low despite a high observed agreement [26]. This was demonstrated in a similar clinical decision making agreement study on aneurysm treatment where multiple intrarater kappa values demonstrated paradoxical low kappa values despite high observed agreement [44].

The κ_G_ statistic that was introduced in 2001 has been shown to be relatively resistant to the Kappa paradox and results in values that are more in keeping with the observed agreeement. This is because it has a less severe correction for chance agreement compared to Cohen’s Kappa [39, 45]. As an example, in our study we will look at subgroups according to infarct cores. We expect that in these situations, decisions will be lopsided in that raters will have a much higher tendency to recommend for EVT for small cores and against it for large cores. We chose to use Gwet’s AC1 statistic for our study as we expect it to be a more robust measure of reliability [43].

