**Methods:**

A total of 30 non-consecutive patients will be selected from our institutional database comprising 3144 cranial CT scans performed for acute stroke symptoms January 2018 to August 2022. The clinical and radiologic data of the 30 patients will be presented in random order to a group of 29 physicians in two separate sessions at least three weeks apart. In each session, the physicians will evaluate each patient once with automated perfusion images and once without. We will use non-overlapping 95% confidence intervals and difference in agreement classification as criteria to suggest a difference between the Gwet AC1 statistics (κ_G_).

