### Survey

Cases will be collected and managed using Microsoft Excel v16.72 and REDCap (Research Electronic Data Capture) electronic data capture tools hosted at the Unity Health- St. Michael’s Hospital. REDCap is a secure, web-based software platform designed to support data capture for research studies, providing 1) an intuitive interface for validated data capture; 2) audit trails for tracking data manipulation and export procedures; 3) automated export procedures for seamless data downloads to common statistical packages; and 4) procedures for data integration and interoperability with external sources [29, 30]. Individual, personalized links were sent to the raters via email. Raters were asked details about their practice: type of hospital affiliation, specialty, years in practice and institutional neuroimaging practices for stroke patients. The full survey is in **S1 Appendix.**

For each of the selected 30 patients the following details will be provided: age, location of occlusion, the NIHSS (National Institutes of Health Stroke Score), time of onset, time of scan, non-perfusion CT neuroimaging (NCCT and CTA). The NCCT scan will be shown in the recommended stroke window settings (35WW 35LL) [31–33]. Doing so ensures that the raters are able to evaluate the scan in a window that is optimized for showing the early ischemic changes important for ASPECTS.

The same 30 cases will be shown again with the same information but with perfusion CT neuroimaging (NCCT, CTA and automated perfusion imaging). Overall, the raters will encounter 60 cases comprised of the same 30 patients shown twice with and without perfusion imaging. The raters will not be informed that these 60 cases are actually the same 30 patients shown twice. To test intra-rater agreement, a second round of rating will be done at least 3 weeks from the submission of the initial reading [34]. The order in which the cases are shown will be the same for the second rating. Apart from not telling the raters, the following measures were also taken to keep the raters realizing that the same 30 cases are being shown:

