### Sample size

We estimated, using kappaSize package in R version 4.2.0 (R Foundation for Statistical Computing, Vienna, Austria), assuming an anticipated kappa value of 0.6 (substantial), that at least 30 cases were necessary for the lower limit of a 95% two–sided confidence interval to remain above 0.45 between at least 6 raters, considering an anticipated prevalence of EVT recommendation of 0.5 [36]. A rule of thumb for agreement studies with binary outcomes is to have at least 10 raters reviewing at least 30–50 patients [25]. While more patients will enable us to provide an even wider spectrum of patients we also want to avoid rater fatigue. For this study we had 60 cases with three questions each. We need to have at least 6 raters based on our sample size computation but will be aiming for at least 10 to follow the current convention.

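### Judging the perfusion versus non-perfusion contrast by non-overlap of two separate 95% CIs plus a category change has low power for a one-category difference in agreement; a CI for the paired AC1 difference should replace it

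*Protocol article*

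**What the plan says.** The Agreement statistics section sets the criterion for comparing AC1 values: "Non-overlapping confidence intervals along with level of agreement will be the factors considered to suggest a potential difference between KG values". The Methods part of the Abstract gives the same rule: "We will use non-overlapping 95% confidence intervals and difference in agreement classification as criteria to suggest a difference". No interval or test for the difference itself is described.

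The design is fully paired. Under Survey: "Overall, the raters will encounter 60 cases comprised of the same 30 patients shown twice with and without perfusion imaging". A second round at least three weeks later supplies the intrarater data.

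The Sample size section concerns the precision of one coefficient, not the contrast. For an anticipated kappa of 0.6 it states that "at least 30 cases were necessary". The precision target behind that number is a lower two-sided 95% limit no worse than 0.45 with six or more raters, taking EVT to be recommended half the time. On rater numbers, the investigators "will be aiming for at least 10 to follow the current convention"; the Abstract gives 29.

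The second and third study questions ask whether interrater and intrarater agreement differ significantly between the two protocols. The Abstract and the Discussion both say that, if reliability does not differ significantly, late-window imaging recommendations may need revision.

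**The concern.** Two 95% intervals can overlap when the difference between the estimates is clearly significant. With equal standard errors, non-overlap requires a gap of 3.92 SE. A 5% test of two independent estimates requires 2.77 SE. When the estimates are positively correlated, as is likely with shared raters and patients, the proper threshold falls further while the overlap threshold stays where it is.

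Low power is not a harmless form of caution in this study. The result that could prompt a change in practice is the null one, and this rule favours the null. A whole-category change in agreement could be present and still be reported as no difference.

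**Working it through.** **Inputs from the protocol article.** Kappa 0.60, lower 95% limit 0.45, prevalence 0.5, at least 6 raters, 30 cases (Sample size). Each agreement category is about 0.20 wide (Agreement statistics). **Assumption:** the correlation r between the two AC1 estimates is not given, so a range is shown.

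**Step 1. The plan's own figure.** A goodness-of-fit interval for binary kappa under the common-correlation model has n = χ² / Σ[(P_j(0.60) − P_j(0.45))² / P_j(0.45)], where P_j is the probability that j of 6 raters recommend EVT.
- One-sided 5% limit: n = 32 (31 with P_j(0.60) in the denominator), close to the stated 30.
- Two-sided 95% limit, as the text specifies: n = 46 (44), which does not match 30.

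The main calculation takes the stated precision at face value; a sensitivity check uses the larger SE that the one-sided reading implies. At prevalence 0.5, chance agreement in AC1 is 2 × 0.5 × 0.5 = 0.5, as for kappa, so carrying the precision over to AC1 is reasonable.

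**Step 2. Thresholds.** SE = (0.60 − 0.45)/1.96 = 0.15/1.96 = 0.077.
- Non-overlap: |d| > 1.96(SE + SE) = 0.30, and 0.30/0.20 = 1.5 categories.
- Paired comparison: |d| > 1.96 × SE × √(2(1 − r)).

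**Step 3. Power for a true difference of 0.20.** With SD(d) = SE√(2(1 − r)), power ≈ Φ((0.20 − threshold)/SD(d)).

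| r | SD(d) | Paired threshold | Power, non-overlap | Power, paired |
|---|---|---|---|---|
| 0 | 0.108 | 0.21 | 18% | 46% |
| 0.3 | 0.091 | 0.18 | 13% | 60% |
| 0.5 | 0.077 | 0.15 | 10% | 74% |
| 0.7 | 0.059 | 0.12 | 5% | 92% |

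The r = 0 row separates the two causes: the overlap rule alone takes power from 46% to 18%, and ignoring the pairing widens the gap as r rises.

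With no true difference, non-overlap at r = 0 needs |z| > 0.30/0.108 = 2.77, a rate of about 0.6%. At r = 0.5 it needs |z| > 3.92, about 0.01%.

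**Step 4. Sensitivity.** On the one-sided reading SE = 0.15/1.645 = 0.091 and non-overlap needs 0.36. Power is then 11% versus 34% at r = 0, and 4% versus 59% at r = 0.5.

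**Step 5. Simulation.** AC1 with its linearised case-level variance and t(29) intervals, 30 cases, 5,000 runs per setting, true difference 0.20. The four values in each cell are for case-signal correlations of 0, 0.7, 0.95 and 1 between protocols; the rule is non-overlap plus a category change. Results for 29 raters:

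| True AC1 pair | Planned rule | Paired comparison |
|---|---|---|
| 0.5 vs 0.7 | 20, 18, 11, 7% | 48, 61, 92, 100% |
| 0.6 vs 0.8 | 24, 22, 16, 12% | 53, 62, 90, 100% |
| 0.7 vs 0.9 | 36, 35, 32, 28% | 64, 71, 89, 100% |

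Over all settings simulated, the rule's power was 5–25% with 6 raters, 5–32% with 10 and 7–36% with 29; paired power was 33–84%, 41–97% and 48–100%. A model with three strata of 10 cases and rater effects (true difference about 0.21; 4,000 runs) gave 13% versus 69% with 10 raters and 17% versus 89% with 29. With no true difference, non-overlap occurred in at most 0.6% of runs, against about 5% for the paired test. The category condition removed almost nothing beyond non-overlap.

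**The case against.** **The wording is tentative.** The rule is said only to suggest a potential difference. That is fair, but the study questions, the Abstract and the Discussion treat the outcome as a statement of significance, and no other criterion is offered.

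**The downstream use is qualified.** The results are to be read with clinical-outcome and cost-effectiveness data, and recommendations only may need to change. This stands: the document does not rest a policy change on this null result alone.

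**A reader might infer that a finding of no difference is all but certain.** The figures do not support that. The 0.20 difference is a reviewer's choice, since the protocol names none, and larger differences are found more often. By the formula a true 0.30 is detected half the time. Simulation of 0.61 versus 0.89 under non-overlap gave 67–72%.

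**A reader might blame the pairing alone.** The r = 0 row shows that much of the loss exists without it.

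**A reader might infer that a change of category label alone would count as a difference, and so produce many false positives near the 0.60/0.61 cut.** Both statements of the rule join the two criteria, so the text does not support that reading.

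**The simulation is not the exact planned analysis.** The protocol plans bias-corrected intervals, whereas the simulation used linearised ones. The correlations and variance components are assumed, and intrarater AC1 was not simulated. The threshold argument does not depend on these choices, but the exact percentages do.

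**Conclusion.** The concern holds. The stated rule does not suit a paired comparison of two AC1 values and is not a 5% test even for unpaired ones. At the protocol's planned precision it needs an observed difference of about 0.30. Its power for a true 0.20 is roughly 5–18%, against 46–92% for a paired comparison, over r from 0 to 0.7. Across the simulated settings it missed a 0.20 difference in 64–95% of studies. These sizes rest on the stated half-width of 0.15, the assumed range of r, and interrater AC1.

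It would go too far to conclude that a paired test cures the problem. With 30 cases and weak correlation, paired power for 0.20 may be only about 35–50%, so a non-significant paired result would not establish equal reliability either.

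**What to change.** In the Abstract and in Agreement statistics, replace the non-overlap and category criteria as follows.

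1. Make the comparison the paired difference, AC1(perfusion) minus AC1(non-perfusion), with a 95% CI, for both interrater and intrarater agreement. Declare a difference when the CI excludes 0.
2. Obtain the CI by a bootstrap that keeps both protocols of each rater–patient pair together, or by the linearised paired variance. For interrater AC1 the latter uses the SD of the 30 within-patient differences in linearised values, divided by √30.
3. For comparisons between rater subgroups, which contain different raters, resample the shared patients jointly.
4. Keep the agreement categories as description only.
5. State that overlapping intervals, or a CI that includes 0, do not show equal reliability. Base the Discussion's conclusion on the range of differences the CI still allows.

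The cost is a few sentences and a short R script. No new cases, raters or readings are needed.

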### Case selection

All included studies will be taken from an institutional database (January 2018- August 2022) of patients undergoing in-house neuroimaging for symptoms of acute ischemic stroke. A team of clinical and research physicians will review the entire database to identify reported large vessel occlusions in patients being scanned for symptoms of stroke from January 2018 to August 2022. The primary author who is a dual trained stroke neurologists and neurointerventionalist will review all the patients that were flagged to determine eligibility for the study. The inclusion criteria will include the following:

Adults aged ≥ 18 years oldStroke onset or last known well time between 6–24 hours prior to start of imaging (late-window stroke)Use of automated perfusion CT (RAPID, iSchemaView, Menlo Park, CA)Confirmed complete large vessel occlusion on CTA involving the following vessels: first segment of the middle cerebral artery (M1), terminal portion of the internal carotid artery (ICA), tandem occlusion of the proximal ICA and either of the occlusions (M1 and terminal ICA)Penumbra size of at least 15cc of perfusion CTMismatch ratio (volume of the entire area affected: core infarct volume) of at least 1.8National Institutes of Health Stroke Score (NIHSS) of 6 or more

Our exclusion criteria were:

Neuroimaging findings reported to be compatible with a chronic occlusionOcclusions located in the distal anterior circulation territory or the posterior circulationMissing clinical dataUnsatisfactory neuroimaging (artifacts, improper timing of contrast, poor quality perfusion studies)

To minimize the paradoxes of Kappa statistics [26, 27], we will include the full range of infarct core sizes: 10 cases with small core (0–49 cc), 10 cases with medium core (50-100cc), 10 cases with large core (>100cc). Sequential, consecutive inclusion of cases will result in an imbalanced distribution as cases of small to moderate cores will likely dominate the selection because the institution is a tertiary referral center that will preferentially transfer those with smaller cores. Evidence for EVT in ELVIS patients with large core is a recent development; thus, all the patients were transferred to our institution during a time when the only positive randomized EVT trials were for small to medium core patients. This would lead to a paradox of high percent agreement (only by chance) but low reliability [26, 27].

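### In the core-size subgroups, κ_G, its agreement label and the difference rule can reflect the EVT proportion alone rather than how reliably raters tell cases apart

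*Protocol article*

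**What the plan says.** Under Agreement statistics, inter-rater and intra-rater agreement on recommending EVT "will be assessed using Gwet’s AC1 (κ_G_) reliability coefficient", "with 95% bias-corrected confidence intervals". The "agreement categories were defined according to Landis and Koch and used to classify the K_G". The decision rule is: "Non-overlapping confidence intervals along with level of agreement will be the factors considered to suggest a potential difference between KG values"; the Abstract gives the same two criteria. The interrater subgroups are "rater specialty, rater experience, infarct core size and time since stoke onset".

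Case selection fixes the strata: "10 cases with small core (0–49 cc), 10 cases with medium core (50-100cc), 10 cases with large core (>100cc". The same section expects clinicians to favour EVT for small cores, advise against it for large cores, and be unsure about medium cores. Agreement statistics repeats this when justifying the coefficient: in the core-size subgroups "raters will have a much higher tendency to recommend for EVT for small cores and against it for large cores". It presents the milder chance correction of κ_G only as a strength in that setting.

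Case selection also explains why core sizes are balanced over the 30 cases: a set dominated by one kind of case could push the agreement statistics up artificially.

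**The concern.** Splitting the 30 cases by core size recreates, in sets of 10, the lopsided mix that the balanced selection was meant to avoid. In such a set κ_G is high whenever most answers go the same way, whether or not raters separate one patient from another within the set. The label and the difference rule inherit this.

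Two readings are then at risk. One is that small or large cores are judged more reliably than medium cores, when the figures may only restate the EVT proportions. The other concerns the article's own question, perfusion versus non-perfusion imaging. If perfusion images shift the threshold for recommending EVT within a stratum, that shift may be reported as a change in reliability. The article asks separately whether the EVT proportion differs between protocols and cites an earlier study in which perfusion imaging lowered the threshold. The Discussion says the reliability result may bear on imaging recommendations.

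**Working it through.** **Inputs from the article.** 10 cases per core-size stratum (Case selection). 29 raters (Abstract), with a planning minimum of 6 and a target of at least 10 (Sample size). 95% confidence intervals; label cut-offs with moderate 0.41–0.60, substantial 0.61–0.80 and excellent above 0.80; the difference rule (Agreement statistics).

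**Assumed.** The article gives no EVT proportion per stratum. I take 0.80–0.95 for small cores, the mirror image for large cores and 0.50 for medium cores, following the direction it states.

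**The plan's own figure.** The 30 cases (kappa 0.6, lower limit 0.45, 6 raters, prevalence 0.5) can be reproduced with a Wald interval and the intraclass-kappa variance: 1.96² × 2(0.4)²(1+5×0.6)² / (6×5) / 0.15² = 3.84 × 0.1707 / 0.0225 = 29.1, so 30. Other standard models give other numbers, and nothing below rests on this. It concerns all 30 cases at prevalence 0.5, the one prevalence at which the problem vanishes.

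**Expected κ_G without case-level signal.** Suppose each rater recommends EVT with probability p for every case in the stratum. Observed agreement is 1−2p(1−p) and the AC1 chance term is 2p(1−p), so

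κ_G = (1−4p(1−p)) / (1−2p(1−p)).

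| p | 2p(1−p) | Observed agreement | κ_G | Label |
|---|---|---|---|---|
| 0.50 | 0.500 | 0.500 | 0/0.500 = 0.00 | slight |
| 0.70 | 0.420 | 0.580 | 0.160/0.580 = 0.28 | fair |
| 0.80 | 0.320 | 0.680 | 0.360/0.680 = 0.53 | moderate |
| 0.85 | 0.255 | 0.745 | 0.490/0.745 = 0.66 | substantial |
| 0.90 | 0.180 | 0.820 | 0.640/0.820 = 0.78 | substantial |
| 0.95 | 0.095 | 0.905 | 0.810/0.905 = 0.895 | excellent |

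The formula is symmetric in p and 1−p. Substantial needs p of about 0.83–0.91, or 0.09–0.17. Fleiss' kappa averages about 0 throughout.

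**How often the label appears.** In simulation with 10 cases, 29 raters and no case-level signal, the label is substantial or better in about 10% of runs at p=0.80, 82–83% at 0.85 and 100% at 0.90.

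**How often the rule fires.** 20,000 runs, linearised AC1 variance over cases, t interval with 9 degrees of freedom; flagged means intervals do not overlap and labels differ. No case-level signal:

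- 0.85 v 0.50: about 100% with 29 raters, 97% with 10, 77% with 6.
- 0.80 v 0.50 and 0.90 v 0.50, 29 raters: about 100%.
- 0.85 v 0.15 and 0.90 v 0.10, 29 raters: about 0.5%.

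A percentile bootstrap over cases gave non-overlap in 100% of runs (0.85 v 0.50) and 1.8% (0.85 v 0.15).

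**Equal case-level signal in both strata.** With intraclass correlation ρ, observed agreement becomes 1−2p(1−p)(1−ρ), so κ_G = (1−2p(1−p)(2−ρ)) / (1−2p(1−p)). At ρ=0.2 this is 0.541/0.745 = 0.73 at p=0.85 and 0.10/0.50 = 0.20 at p=0.50. At ρ=0.4 it is 0.592/0.745 = 0.79 and 0.20/0.50 = 0.40. The gap persists although ρ is identical, but the intervals widen. For 0.85 v 0.50 with 29 raters, flagging falls to about 66% at ρ=0.2, 26% at 0.4 and 12% at 0.6.

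**Perfusion v non-perfusion within a stratum.** If imaging moves p from 0.85 to 0.70, κ_G moves from 0.66 to 0.28. With 29 raters the rule flags this in about 88% of runs with no case-level signal, and about 15% at ρ=0.2. The two protocols were simulated as independent sets.

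**The case against.** The best defence is about what is being measured. The article asks whether raters agree on a recommendation and whether decisions are repeatable. At p=0.90, 82% of rater pairs agree; at 0.50, half do. That is a genuine difference in agreement, and raters who answer differently for small and medium cores are responding to core size. The article also chose κ_G openly for its milder chance correction, and the kappa statistics it avoids behave badly in lopsided strata. All this stands, and it is why κ_G should stay. It does not answer the point entirely, because the article's own case-selection argument rejects agreement raised by a lopsided mix.

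A reader might infer more than the documents support:

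- *That core sizes would be declared different almost every time.* Not so for small versus large cores, the pair contrasted in "raters will have a much higher tendency to recommend for EVT for small cores and against it for large cores": mirror-image proportions give equal κ_G.
- *That the rule cannot discriminate at all.* Flagging falls steeply once there is real case-level signal.
- *That a substantial label is assured.* At p=0.80 the usual label is moderate.
- *That the study sets out to test one core size against another.* The Study questions compare imaging protocols. A contrast between core sizes is implied only by the general wording of the rule, which speaks of suggesting a potential difference.

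**Conclusion.** The point holds in limited form. In the strata the article itself expects to be lopsided, the κ_G level, its label and the difference rule can reflect the EVT proportion alone. The expected κ_G values are exact algebra. The flagging rates depend on assumed proportions and on the amount of case-level signal: for a lopsided versus a balanced stratum with 29 raters, from about 100% with none to about 26% at intraclass correlation 0.4. The imaging comparison is exposed in the same way if imaging shifts the EVT proportion, strongly with no signal (about 88%) and weakly with modest signal (about 15%). Choosing κ_G is not itself an error. What needs limiting is the conclusion drawn from its label and intervals when EVT proportions differ.

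**What to change.** Keep κ_G. For each subgroup and imaging protocol, report beside it:

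- the EVT proportion;
- observed agreement;
- agreement on recommending and on not recommending EVT, separately;
- Fleiss' kappa;
- the κ_G expected from independent ratings at that EVT proportion.

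Add one sentence to Agreement statistics: where EVT proportions clearly differ between the groups compared, a difference in κ_G label or intervals will not on its own be read as a difference in reliability, but described as a difference in agreement that may reflect the EVT proportion. A general ban on the labels is not needed.

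The cost is a few more table columns from the same data, and some weaker subgroup claims. Fleiss' kappa is imprecise in lopsided strata, so it serves as a companion to κ_G and not a replacement.
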